## Abstract

**Abstract:**

**Introduction:**

Observational data are increasingly used to study and draw causal inferences about the effects of treatments. Target trial emulation (TTE) is a framework for mitigating biases in causal investigations through specification of an observational study, targeting a specific causal research question, based on a real or hypothetical randomised controlled trial. Investigations into the effects of treatment discontinuation are of growing interest and particularly relevant in cystic fibrosis (CF), where treatment burden is high and new transformative therapies are becoming widespread. We aim to use the TTE framework to investigate the effect of discontinuation of inhaled corticosteroids (ICS) on clinical outcomes in people with CF. Our observational emulation will be based on the CF WISE (Withdrawal of Inhaled Steroids Evaluation) trial (PMID:16556691).

**Methods and analysis:**

Two study designs proposed for investigating treatment effects using observational data are the prevalent new-user design and the sequential trials design. Each design uses different but related methods to address similar causal questions; however, the comparability between them remains uncertain. We will conduct a population-based cohort study using data from the UK CF Registry between January 2016 and June 2018 and apply these designs. We will specify the target trial protocol for each study design. Estimates for the causal effects of discontinuing ICS will be obtained and compared with those from the CF-WISE trial.

**Ethics and dissemination:**

This study has received approval from the UK CF Registry Research Committee for both the research and access to data. Ethical approval has also been granted by the LSHTM Ethics Committee. The UK CF Registry has NHS Research Ethics Committee approval (REC reference: 24/EE/0012). The findings from this project will be submitted to peer-reviewed journals and presented at academic conferences.

STRENGTHS AND LIMITATIONS OF THIS STUDYThis protocol describes the first real-world cohort study on treatment discontinuation in people with cystic fibrosis (CF).The analysis will use registry data with near-whole population coverage for people with CF in the UK.The study will compare two causal study designs—the prevalent new-user design and sequential trials design—under the target trial emulation framework, with findings benchmarked against a CF trial.Both study designs have been shown to mitigate measured confounding and avoidable design-related biases such as selection bias and immortal time bias.Limitations include potential for errors in treatment discontinuation dates and lack of information on adherence.

## Introduction

 The target trial emulation (TTE) framework has been proposed to identify and avoid potential biases when estimating the causal effects of treatment using observational data. The strategy entails specifying protocol components of a real or hypothetical randomised controlled trial (RCT) (the ‘target trial’), including the causal estimand of interest, and detailing the emulation of this using the available observational data. The framework has the potential to minimise common time-related biases in pharmacoepidemiology and provides an opportunity to validly address a breadth of research questions, including about comparative effectiveness and treatment discontinuation.^1^,^4^

TTE has been adopted in many therapeutic areas, including cystic fibrosis (CF).^5^,^7^ CF is a life-shortening condition, caused by mutations in the CF transmembrane conductance regulator (CFTR) gene, which affects multiple organ systems, including the lungs, liver, digestive tract and reproductive organs. There are over 11 000 people in the UK living with CF.^8 9^ People with CF often face substantial treatment burden, requiring complicated and time-consuming treatment plans daily to maintain their health.^10^ This includes multiple different daily oral and inhaled therapies on a long-term basis as an integral component of management for the majority of people with CF.

Inhaled corticosteroids (ICS) are commonly used by people with CF, with the purported aim of targeting inflammation and/or symptoms of wheeze. However, the current evidence for risks and benefits of ICS in CF is uncertain, with known adverse effects on growth and adrenal function.^11^ A Cochrane review of ICS effectiveness in people with CF concluded that none of the currently published trials could conclude effectiveness at reducing lung inflammation; despite this, ICS are still widely prescribed.^9^ The only trial included which was found to have a low risk of bias was the CF-WISE (Withdrawal of Inhaled Steroids Evaluation) trial (PMID:16556691).^11 12^ CF-WISE investigated the effect of discontinuing ICS on risk of pulmonary exacerbation in the UK and concluded that it was safe for most patients to discontinue.^12^

This study aims to estimate the causal effects of discontinuing ICS on clinical outcomes in people with CF using ICS, using observational data from the UK CF Registry to emulate a target trial based on the CF-WISE trial (the ‘index trial’). Studying treatment discontinuation effects in observational data is challenging, with a notable evidence gap around the optimal methodological approach. Using the TTE framework, we will therefore consider two distinct study designs—the prevalent new-user design (PNUD) and the sequential trials design—and empirically compare the results between these designs and the published CF-WISE trial findings.

This study will also provide a framework for further trial emulations in the contemporaneous era where there is now widespread use of CFTR modulator treatments which are disease modifying and transforming clinical outcomes.^8 13^ This will contribute to the evidence base for medication use for the CF community in a time of rapid change in the treatment landscape. It will provide insight into the relative strengths and weaknesses of the two approaches (PNUD and sequential trials design), which will inform the wider field of treatment deprescribing. This will contribute to better understanding and improved accessibility of causal study designs for treatment discontinuation, to support further application of these designs and the TTE framework, including questions not answered by RCTs such as the longer-term effects of ICS discontinuation.

This study protocol is written using the HARmonised Protocol Template to Enhance Reproducibility guidelines.^14^

## Research aim and objectives

### Research aim

We aim to estimate the causal effects of discontinuing ICS on clinical outcomes (pulmonary exacerbations and lung function) in people with CF using two different study designs in observational data.

### Objectives

To emulate a target trial using UK CF Registry data based on a previously conducted RCT, CF-WISE and assess whether the findings of the emulations are consistent with the results from the CF-WISE trial.To apply the PNUD and sequential trials design to emulate a discontinuation trial, to establish the estimands being targeted under the two designs, compare the results and interpret any differences.

## Methods and analysis

### Data source

The UK CF Registry (UKCFR) is a centralised national database sponsored and managed by the CF Trust, which collects real-world data from all specialist CF centres in the UK.^15^ It holds data on an estimated 99% of the UK CF population covering demographic and longitudinal clinical data and was highlighted by the UK National Institute for Health and Care Excellence real-world evidence framework as an exemplar data source for evidence generation.^16^

Data collection for the UKCFR began in 1996 and is primarily structured around annual review visits, taking place approximately 1 year apart. In addition, demographic data including sex, ethnicity, diagnosis data and genotype are collected at enrolment into the Registry and usually remain time-invariant. Information is captured annually on events or conditions that have happened since the previous annual review, including complications, infections, treatments and hospital admissions. Other information collected at the date of each annual review includes results from pulmonary function tests, weight and height. Extracts of data recorded at annual reviews are provided to researchers for approved projects. In 2016 variable domains were added, including exact start and stop dates of medications.

### The index trial: CF-WISE

CF-WISE was a double-blind RCT investigating the safety of withdrawing ICS in people with CF.^12^ Participants were recruited from 18 UK CF centres and the trial was carried out between November 2001 and July 2004. Participants taking fluticasone propionate (a specific ICS) were randomised to either discontinuation or continued use and followed up for 6 months, with time to first pulmonary exacerbation as the primary outcome.^12^ There was no evidence of a change in time to first exacerbation with HR (95% CI) 1.07 (0.68 to 1.70) and no change in secondary outcomes for fluticasone propionate versus placebo and based on this, it was concluded likely safe for most patients to withdraw from the medication.^12^ Despite this, ICS use remains common in people with CF with 20% of adults in the UK being prescribed this treatment.^9^

### Study design

We will use UKCFR data to conduct an emulation of a target trial based on the CF-WISE trial. This will be done using two study designs: (1) the PNUD and (2) the sequential trials design.^3 17^ The two study designs use distinct but related approaches to making use of observational data and applying statistical analyses to estimate causal effects, with control for measured confounding and time-related biases being at both design and analysis phases.^3 17^ The data used for these emulations will be from 2016 to 2018, chosen intentionally based on data quality and completeness in the UKCFR data and being in the pre-CFTR modulators era. Table 1 specifies the protocol components of the index trial (CF-WISE), the corresponding target trial (hypothetical RCT we would undertake if it were feasible) and how each element of the target trial will be emulated using UKCFR data.

**Table 1 T1:** Specification and emulation of a target trial of deprescribing from inhaled corticosteroids in the UKCFR

Protocol component	CF-WISE (index randomised trial*)	Target trial	Target trial emulation using UKCFR
Eligibility criteria	People diagnosed with CF aged ≥6 years, with FEV _1_≥40% predicted, sustained ICS use ≥3 months. Recruitment period November 2001 and July 2004. Excluded are people who used oral corticosteroids, high-dose ICS or intravenous antibiotics in the 4 weeks prior to treatment assignment.	Same as CF-WISE, except study period is between January 2016 and June 2018. This period reflects a balance between data quality and completeness in UKCFR and prior to the widespread introduction of CFTR modulators.	Prevalent new-user design*:* Same as target trial, except ICS dosage was not recorded. Individuals are eligible for the base cohort (see *Study design*) on the earliest date within the study period that they meet all eligibility criteria. Sequential trials design: Same as target trial, except ICS dosage not recorded. Successive regularly spaced ‘trials’, with eligibility criteria redefined based on most recent data if available.
Treatment strategies	Following a 2-month run-in period receiving fluticasone propionate, participants either: continue to take fluticasone, or switch to taking placebo.	Participants either: continue to take ICS (any ICS, not limited to fluticasone propionate) for the duration of follow-up, or discontinue ICS and remain not taking it for the duration of follow-up.	Prevalent new-user design: Same as target trial, with information on (dis)continuation obtained using prescription start and stop dates. Sequential trials design: Same as the PNUD.
Assignment procedures	Randomisation to treatment strategy Investigators and participants blinded to assignment.	Same as CF-WISE.	Prevalent new-user design: For each discontinuer, comparators will be selected into time-based exposure sets that correspond to each ICS discontinuer. Comparators within each exposure set will then be reweighted to resemble the discontinuers. Sequential trials design: Sequence of artificial ‘trials’, with discontinuers and continuers defined within each regularly spaced ‘trial’. Potential for re-use of continuers across multiple trials. Confounder adjustment is through regression. In the absence of randomisation, treatment assignment is assumed to be random conditional on ICS treatment history and the measured covariates specified in *Covariates*.
Follow-up and index date	Follow-up starts at randomisation and ends at loss to follow-up, meeting criteria for early trial withdrawal, or 6 months of follow-up, whichever occurs first.	Same as CF-WISE	Prevalent new-user design: Follow-up starts at date of ICS discontinuation for both the discontinuers and the reweighted continuers. Sequential trials design: Follow-up starts at the date of ICS discontinuation for the discontinuers and the date of the start of each successive ‘trial’ for the continuers in that trial. For the primary outcome, individuals will be followed up to first pulmonary exacerbation, death, transplant or 6 months after treatment assignment, whichever occurs first. For information on follow-up for secondary outcomes (lung function) see online supplemental material appendix 1.
Outcomes	Primary: time to first pulmonary exacerbation Secondary: (i) lung function change (FEV_1_ and FVC), (ii) new/unplanned courses of intravenous antibiotics and (iii) rescue bronchodilator usage	Same as CF-WISE	Primary: same as target trial, with different definition for pulmonary exacerbation; defined as a course of hospital or home intravenous antibiotics (see *Outcomes*). Secondary: (i) mean change in FEV_1_% predicted and FVC% predicted. Secondary outcomes (ii) and (iii) will not be assessed due to similarity of UKCFR definitions for intravenous antibiotic courses and pulmonary exacerbation and inability to define rescue bronchodilator use, respectively.
Causal contrasts	Intention-to-treat	Same as CF-WISE	Observational analogue of intention-to-treat and per-protocol
Statistical analysis	For primary outcome, a Cox proportional hazard regression was used. The Wilcoxon rank sum test was used to compare % change in lung function. ORs or relative risks were estimated to compare categorical outcomes (ii and iii). Prespecified subgroup analyses for age, atopic status, dose of ICS, baseline FEV_1_ and *Pseudomonas aeruginosa* infection status.	Same as CF-WISE	Prevalent new-user design: Weighted Cox proportional hazards regression will be used to estimate HRs and 95% CIs. Marginal survival curves and risk difference at 6 months will be estimated. Sequential trials design: Adjusted Cox proportional hazards regression to estimate HRs and 95% CIs. Marginal survival curves and risk difference at 6 months estimated using standardisation. For both designs, intention to treat and per-protocol estimates will be calculated, the latter using inverse probability of censoring weights to account for informative censoring where individuals switch from assigned treatment during follow-up. For information on analysis for secondary outcomes (lung function) see online supplemental material appendix 1 .

* When the target trial is based on an existing RCT this corresponding RCT is termed the reference or index trial. Some aspects of the index trial and target trial may differ because it is not possible to emulate them in observational data, and separating the index and target trials can help to highlight where any differences in findings from the emulated trial compared with the index trial may arise.^48 49^

CFTR, cystic fibrosis transmembrane conductance regulator; CF WISE, Cystic Fibrosis Withdrawal of Inhaled Steroids Evaluation; FEV1, forced expiratory volume in 1 s; FVC, forced vital capacity; ICS, inhaled corticosteroids; PNUD, prevalent new-user design; RCT, randomised controlled trial; UKCFR, UK Cystic Fibrosis Registry.

#### Prevalent new-user design

The PNUD extends the scope of inference of the incident new-user design to include switchers to a (typically new) study drug from an existing comparator drug (ie, prevalent new-users).^17 18^ Beyond the switching context, PNUD can be used to study causal questions surrounding treatment discontinuation; here, the drug discontinuer is conceptualised as the ‘prevalent new-user’ and the continuer is the comparator.^19 20^

The first step of the PNUD will be to define a base cohort with respect to pre-defined eligibility criteria in the study period (see *Inclusion and exclusion criteria*, table 1). So-called ‘exposure sets’ will then be defined, each of which includes a discontinuer plus people remaining on ICS (continuers) who are similar to the discontinuer in terms of being observed within a similar calendar period and their ICS exposure history. Figures1  2 illustrate the formation of these exposure sets, each comprising a discontinuer and a pool of comparators (continuers). Treatment discontinuation (and continuation) will be determined based on treatment start and stop dates as recorded in the UKCFR. The analysis then involves reweighting continuers so that the comparators resemble the discontinuer with respect to measured baseline covariates (detailed in *Main analysis*).

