**Figure 1 F1:**
[figure not shown]
Study diagrams showing the selection of comparators and formation of analysis cohorts for emulating a target trial of discontinuation of inhaled corticosteroids (ICS) using the UK Cystic Fibrosis Registry (UKCFR), using the prevalent new-user design. Dotted green lines represent time an individual is taking ICS but not yet eligible for inclusion in the base cohort, solid green lines represent time an individual is taking ICS after more than 3 months of initial use, dotted blue lines represent time an individual is no longer taking ICS. (a) Five example individuals who meet the eligibility criteria for inclusion in the base cohort, where 1–3 discontinue ICS in the study period. (b) The criteria for being in each of the discontinuer’s exposure sets in calendar time (6 months either side date of discontinuation). (c) Individuals 2 and 5 are included in individual 1’s exposure set due to similarity in both calendar time and ICS exposure history. (d) Only individual 5 would be included in individual 2’s exposure set and (e) only individual 4 would be included in individual 3’s exposure set.

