**Figure 2 F2:**
[figure not shown]
Study diagram showing the selection of comparators and formation of analysis cohorts for emulating a target trial of discontinuation of inhaled corticosteroids using the UK Cystic Fibrosis Registry (UKCFR), using the prevalent new-user design (PNUD) on an alternative time scale (time since eligibility). This diagram displays five example individuals who meet eligibility criteria for inclusion in the base cohort (the same as in figure 1), with the exposure sets on a time since eligibility time scale (a PNUD visualisation commonly used to display the organisation of prevalent new-users and comparators in the analysis cohort).^17^

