### Target trial emulation

#### Time periods

##### Prevalent new-user design

We specify a study eligibility period between 1 January 2016 and 30 June 2018 since exact medication start and stopping dates are available in the UKCFR from 2016 onwards. The end of the eligibility period is chosen to ensure the study follow-up ends before (1) highly effective CFTR modulator therapies became widely prescribed in the UK and (2) the SARS-CoV-2 pandemic affected care pathways and data collection.^23^ Individuals who meet the eligibility criteria within this period will form the base cohort. For comparison, participants were recruited between November 2001 and July 2004 in CF-WISE.^12^

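### Exchangeability is assumed conditional on ICS treatment history, but neither design's listed adjustment set contains an ICS duration term, and the history metric for the PNUD exposure sets is undefined

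*Protocol article*

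**What the plan says.** The identifying assumption is in Table 1 (Assignment procedures): without randomisation, "treatment assignment is assumed to be random conditional on ICS treatment history and the measured covariates" listed in the Covariates section. ICS history is thus named as something additional to that list.

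The Variables section says that variable specifications are the same in both designs. The Covariates section lists demographic, clinical, infection and co-treatment variables. Its only elapsed-time term is the time from the previous annual review to time zero. ICS duration is not listed.

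Under Main analysis, the PNUD propensity score model takes those covariates plus a term called time, which is not defined. The sequential-trials Cox models adjust for the baseline confounders. The censoring models use the same baseline covariates.

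For the PNUD sets, the Study design section says that continuers are to be "similar to the discontinuer in terms of being observed within a similar calendar period and their ICS exposure history". The Figure 1 caption fixes the calendar part at "6 months either side date of discontinuation". No equivalent is given for history. The Figure 2 caption redraws the same people "with the exposure sets on a time since eligibility time scale" and calls this "a PNUD visualisation commonly used to display the organisation of prevalent new-users and comparators in the analysis cohort". Table 1 places base-cohort entry "on the earliest date within the study period that they meet all eligibility criteria", and the Time periods section gives the limits: "We specify a study eligibility period between 1 January 2016 and 30 June 2018". On the data, the Data source section says: "In 2016 variable domains were added, including exact start and stop dates of medications".

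**The concern.** How long someone has used ICS plausibly affects both the decision to stop (a short trial of therapy that failed is not the same as established maintenance) and the exacerbation risk after stopping. The plan itself treats history as necessary for exchangeability. If it is not in the models, the stated assumption and the stated adjustment do not agree, and the sequential-trials estimate is exposed to confounding that the plan says it has conditioned on.

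The comparison of the two designs is also at stake, and it is a stated objective. Matching on prior exposure is one of the features that distinguish the PNUD. If one design handles history in an unspecified way and the other not at all, a difference between their estimates could reflect unequal adjustment rather than the designs or their estimands.

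**Working it through.** The article gives no figure to reproduce. The check has three parts.

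**1. Assumption against adjustment set.**
- Table 1 conditions on ICS treatment history and the listed covariates.
- The Covariates section has no ICS duration or history term, and the Variables section makes the list common to both designs.
- In the sequential trials, eligibility requires more than 3 months of ICS, with no upper limit or strata. Beyond that, nothing stated in the outcome or censoring models conditions on history.
- In the PNUD, history could enter through set formation or through the undefined time term, but neither is specified.

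**2. What the only scale shown would measure.** Inputs from the article: the eligibility period runs from 1 January 2016 to 30 June 2018; base-cohort entry is the earliest qualifying date within it; prior ICS use must exceed 3 months (taken as 91 days); and continuers take the discontinuer's stop date as time zero. The ICS start dates and the time zero below are illustrative assumptions.

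Eligibility date = latest of (1 January 2016; ICS start + 91 days; date the other criteria are met). Clock = time zero − eligibility date. A month is 30.4375 days.

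The largest possible clock value is 911 days, or 911 / 30.4375 = 29.9 months. For time zero on 1 January 2017:

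| ICS start | Other criteria met by | Eligibility date | Clock (months) | True duration (months) |
|---|---|---|---|---|
| 1 Jan 2006 | 1 Jan 2016 | 1 Jan 2016 | 12.0 | 132 |
| 1 Jan 2011 | 1 Jan 2016 | 1 Jan 2016 | 12.0 | 72 |
| 1 Jan 2014 | 1 Jan 2016 | 1 Jan 2016 | 12.0 | 36 |
| 1 Oct 2015 | 1 Jan 2016 | 1 Jan 2016 | 12.0 | 15 |
| 1 Jan 2016 | 1 Jan 2016 | 1 Apr 2016 | 9.0 | 12 |
| 1 Apr 2016 | 1 Jan 2016 | 1 Jul 2016 | 6.0 | 9 |
| 1 Jan 2006 | 1 Jul 2016 | 1 Jul 2016 | 6.0 | 132 |

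The first four rows cannot be told apart. The last row shows a long-term user, made eligible late by another criterion, sharing a value with a user of 9 months. The fifth and sixth rows show the scale working: for people who start within the study period and meet the other criteria, the clock is true duration minus about 3 months.

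**3. How many people could be affected.** The article does not say. As an illustration only, assume that elapsed ICS durations are exponential with mean τ years and that time zeros are spread evenly over the 2.5 years. The share who began before 2016 is then (τ / 2.5) × (1 − exp(−2.5 / τ)):
- τ = 1: 0.37
- τ = 3: 0.68
- τ = 5: 0.79
- τ = 8: 0.86

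These shares include late-2015 starters, who lose almost nothing. They show how strongly the answer depends on an unknown, and they say nothing about imbalance between arms or bias in the HR.

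**The case against.** A reader might infer that the plan matches on a clock starting in January 2016. The article does not say so. Time since eligibility appears only in the Figure 2 caption, as an alternative scale for display. The text and the Figure 1 caption name ICS exposure history as a criterion separate from calendar time. Figure 1 draws ICS use before eligibility and refers to initial use. Checking more than 3 months of use on 1 January 2016 also needs some information from before that date. The figures themselves are not available here.

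A reader might also infer that a usable pre-2016 history exists and is being ignored. Neither half is supported. The Data source section says that date fields were added in 2016, not that they hold no earlier start dates. It says that treatments are captured annually, but not since when, or how completely, ICS was recorded. The study years were chosen partly for data quality and completeness.

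Finally, a metric and tolerance are details that an article may leave to a fuller document, and the supplementary appendix is not shown. The comparison of designs also covers estimands, cohort definitions, interpretability and computational efficiency, so it does not rest on duration matching alone.

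All of this stands against the stronger readings. It does not remove the mismatch between Table 1 and the Covariates section, because the article makes both statements and the mismatch does not depend on Figure 2. The Limitations section covers the accuracy of start and stop dates and adherence, but not ICS use before 2016.

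**Conclusion.** The point holds in limited form and should be settled before analysis. The stated identifying assumption includes ICS treatment history and the stated adjustment set does not. For the sequential trials this follows directly from the text. For the PNUD it is conditional: history is a matching criterion without a metric, and the only scale shown would give one common value to everyone already on ICS and otherwise eligible on 1 January 2016.

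The collapse would not reach every pair of long-term and recent users. It concerns people on ICS before 2016, and those made eligible late by another criterion. Its size cannot be stated without the share of the 536 discontinuers who began before 2016; that count was itself taken before the other exclusions. The documents do not show that the HR is biased, or that the PNUD loses its advantage.

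**What to change.** Define prior ICS duration at time zero as a variable common to both designs. Use recorded start dates where they are held. Otherwise, use earlier annual-review ICS records after checking their coverage and completeness. The Sensitivity analyses section already plans to use an annual-review ICS field, so this source is not foreign to the study.

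Include the variable in bands (for example 0–1, 2–4, and 5 or more consecutive prior reviews with ICS recorded):
- in the PNUD propensity score model, and in set formation where numbers allow, with the metric and tolerance stated;
- in the sequential-trials outcome and censoring models. The PNUD censoring model follows, since it shares the propensity score covariates.

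Define the time term in the propensity score model, and report how many discontinuers began ICS before 2016. If pre-2016 history proves unusable, state the truncation as a limitation and amend the Table 1 assumption to what is actually conditioned on.

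The cost is one derived variable and possibly a request for earlier fields from the same registry. Duration before 2016 would be coarse, and banding would slightly reduce the comparators per set.
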